**Objectives:**

Primary:

- To assess the number of re-hospitalizations at 30 and 60 days post discharge with pharmacogenetic testing and YouScript® Personalized Prescribing System
- To assess the number of Emergency Department visits at 30 and 60 days post discharge with pharmacogenetic testing and YouScript® Personalized Prescribing system

Exploratory:

- To assess time to first re-hospitalization.
- To assess time to first Emergency Department visit.
- To assess the impact of genetic testing on overall status according to OASIS M1034 at 30 and 60 days post discharge.
- To assess the impact of genetic testing on frequency of pain according to OASIS M1242 at 30 and 60 days post discharge.
- To assess the impact of genetic testing on frequency of confusion according to OASIS M1710 at 30 and 60 days post discharge.
- To assess the impact of genetic testing on frequency of anxiety

according to OASIS M1720 at 30 and 60 days post discharge.

- To assess the impact of genetic testing on depression according to PHQ-2 at 30 and 60 days post discharge.
- To assess the impact of genetic testing on frequency of disruptive behavior according to OASIS M1745 at 30 and 60 days post discharge.
- To assess the impact of genetic testing on the frequency of ADL and IADL assistance according to OASIS M2110 at 30 and 60 days post discharge.
- To assess whether YouScript® testing decreases falls
- To assess the proportion of YouScript® Personalized Prescribing System recommendations accepted by the study pharmacist and passed on to clinicians.
- To assess the proportion of study pharmacist recommendations acted on by clinicians.

**Sample size** 100 patients (50 intervention, 50 controls)

**Population:** The study population consists of patients aged 65 and older who are currently enrolled in home health and are presently taking or initiating treatment with at least one oral form of medication with a significant drug-drug or drug-gene interaction as defined by FDA boxed warning, FDA cautionary labeling, clinical literature or a YouScript® algorithm-predicted significant effect.

Those meeting eligibility criteria will be prospectively enrolled in either the “tested” group and undergo YouScript® testing or “untested” group and not undergo YouScript® testing.

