**Description of Intervention:** Patients in the “tested” group will receive genetic testing. The study pharmacist will review drug-drug, drug-gene, and drug-drug-gene interactions using YouScript® Personalized Prescribing System to provide drug therapy recommendations to prescribers.

**Estimated Time to Complete Enrollment:** Up to 20 weeks (5+ months)

**Subject Participation Duration:** Each patient will be followed for 60 days from date of admission to home health

**Total Study Duration:** Up to 8 months, depending on the rate of accrual

**Figure 1:** Schematic of Study Design.

[figure not shown]

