### **3.5 Retention Plan**

Subjects who are enrolled in the study and are discharged from home health prior to the initial 60 days will be contacted via telephone to encourage retention.

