Re-hospitalizations and dates of admission are manually recorded, by a member of the home health staff, on a white board displayed in the home health office. PI will manually enter the re-hospitalizations and time to first re-hospitalization on the data entry form for each patient.

Nurses will report ED visits, falls, and adverse drug reactions to PI as well as document in patient chart. PI will manually enter the information into the data entry form.

Additionally, for those patients who received the intervention, the study pharmacist and prescribers will be asked about impact of YouScript® testing on clinical decision-making.

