## **7 STATISTICAL CONSIDERATIONS**

The statistical analysis will include the comparison of the YouScript® and control groups the primary and exploratory outcomes. Poisson regression will be used to compare the number of re-hospitalizations at 30 days, the number of re-hospitalizations at 60 days, the number of ED visits at 30 days, the number of ED visits at 60 days and the number of falls. The log-rank test will be used to compare the time to the first re-hospitalization and the time to the first ER visit. OASIS and PHQ-2 scores will be compared using the Wilcoxon rank sum test. The chi-squared test or the Fisher's exact test (as needed) will be used to compare the proportion of cases with acceptance by the study pharmacist and passing on to clinicians and the proportions of recommendations acted on by clinicians. Calculations will be carried out in R (Vienna, Austria). All tests will be two-sided.  $P < 0.05$  will be used to denote statistical significance. As the study is designed as a pilot, tests will not be adjusted for multiple comparisons.

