### Statistical analysis plan section from the trial protocol

*Taken from section number 7, "Statistical considerations"*

The statistical analysis will include the comparison of the YouScript and control groups the primary and exploratory outcomes. Poisson regression will be used to compare the number of re-hospitalizations at 30 days, the number of re-hospitalizations at 60 days, the number of ED visits at 30 days, the number of ED visits at 60 days and the number of falls. The log-rank test will be used to compare the time to the first re-hospitalization and the time to the first ER visit. OASIS and PHQ-2 scores will be compared using the Wilcoxon rank sum test. The chi-squared test or the Fisher's exact test (as needed) will be used to compare the proportion of cases with acceptance by the study pharmacist and passing on to clinicians and the proportions of recommendations acted on by clinicians. Calculations will be carried out in R (Vienna, Austria). All tests will be two-sided.  $P < 0.05$  will be used to denote statistical significance. As the study is designed as a pilot, tests will not be adjusted for multiple comparisons.

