### **March 24, 2016 Amendments to statistical plan made after study completion**

1. Three outcomes were added post-hoc:

- A. Composite of re-hospitalizations, ER visits and deaths (analyzed as counts at 30 days, 60 days and time to the first event)
- B. Composite of re-hospitalizations and ER visits (analyzed as counts at 30 days, 60 days and time to the first event)
- C. Death by day 60 of the study (analyzed as binary)

2. Two planned outcomes were not compared:

- A. The proportion of cases with acceptance by the study pharmacist and passing on to clinicians
- B. The proportions of recommendations acted on by clinicians.

The comparison did not make sense as these two outcomes applied only to the intervention and not to the control group. In the final analysis the estimated proportions for the intervention were presented.

3. To avoid inappropriate use of Poisson regression we tested for over-dispersion in all Poisson models. In cases when the null hypothesis of no over-dispersion was rejected ( $p < 0.05$ ) we used the negative binomial regression instead of the Poisson regression. This tended to result in appropriately less over-optimistic estimates of the variance.

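### Events after home-health discharge have no stated capture route and the count models have no exposure term, so counts can be truncated and, if observed time differs by arm, the rate ratio is biased

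*Combined protocol and SAP*

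**What the plan says.** The Protocol Summary promises a fixed window: "Each patient will be followed for 60 days from date of admission to home health". The sources named for the two primary outcomes sit inside the home health agency. Under Section 5.1, re-hospitalizations are "manually recorded, by a member of the home health staff, on a white board displayed in the home health office", and the PI copies them to the data form. For the other events, "Nurses will report ED visits, falls, and adverse drug reactions to PI as well as document in patient chart". Appendix A adds abstraction of resource use from the patient chart at Days 30 and 60. No hospital record, claims source or structured patient interview is named.

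Section 3.5 accepts that service may end early: those "discharged from home health prior to the initial 60 days will be contacted via telephone to encourage retention". It specifies no outcome questions, call dates or record retrieval. Section 3.6 replaces withdrawn patients but does not say how their partial follow-up is analysed.

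On analysis, Section 7 (repeated in the SAP extract) says "Poisson regression will be used to compare the number of re-hospitalizations at 30 days", and treats the 60-day counts, ED visits and falls in the same way. No offset, person-time or rule for incomplete follow-up is stated, and the log-rank tests have no censoring rule. The March 2016 amendment returns to these models to deal with over-dispersion. It also adds death by Day 60 and two composites, one of which includes death. It adds no exposure term.

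**The concern.** Once a patient is off service, the stated sources (nurse visits, agency chart, office white board) have no described way of learning about an admission or ED visit. Events before exit are counted and later ones may not be, yet the model treats the count as covering the full window. The patient's count is then truncated, with nothing in the analysis to show it.

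This matters for the comparison only if truncation differs by arm. Randomization balances patients at entry. It does not balance length of service, death or reporting afterwards, and the trial is open-label with a PI who holds the allocation list and also transcribes the outcomes. If tested patients left service sooner, testing would look protective without preventing an admission. If they stayed longer, a real benefit would be diluted. Switching to negative binomial regression, as the amendment allows, changes the variance and not this.

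**Working it through.** **Inputs from the documents.** 50 patients per arm (Protocol Summary); 60-day window; significance at P < 0.05, and "All tests will be two-sided" (Section 7). The documents give no event rate, exit rate, effect size or power, so there is no planned figure to reproduce. Everything below rests on stated assumptions.

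**Step 1: expected bias at Day 60.** Assume a constant event rate, exit unrelated to event risk, and no capture after exit. Let f be the share leaving early, at a mean of Day 30.

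- Mean observed days: D = 60 − 30f.
- Expected count ratio without an offset = true rate ratio × D(tested) / D(control).

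| Leaving early, tested / control | Mean observed days | Factor | True 1.00 reads | True 0.70 reads |
|---|---|---|---|---|
| 20% / 20% | 54 / 54 | 1.000 | 1.00 | 0.70 |
| 40% / 40% | 48 / 48 | 1.000 | 1.00 | 0.70 |
| 30% / 20% | 51 / 54 | 0.944 | 0.94 | 0.66 |
| 40% / 20% | 48 / 54 | 0.889 | 0.89 | 0.62 |
| 50% / 20% | 45 / 54 | 0.833 | 0.83 | 0.58 |
| 20% / 40% | 54 / 48 | 1.125 | 1.13 | 0.79 |

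With log(observed days) as an offset the factor cancels.

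**Step 2: the Day 30 counts.** These are less exposed. With exits uniform over Days 1 to 59, half fall before Day 30, at a mean of Day 15.5, so each of those loses 14.5 days. Mean observed days within the first 30 are 30 − 0.5 × 14.5 × f = 30 − 7.25f. At 40% / 20% this gives 27.10 / 28.55 = 0.95, against 0.89 at Day 60.

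**Step 3: simulation.** 50 per arm, assumed control mean 0.6 events per 60 days, exits uniform on Days 1 to 59 and non-informative, 3,000 runs per scenario, true ratio 1.00.

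| Exit, tested / control | Ratio, no offset | Type I error, no offset | Ratio, offset | Type I error, offset |
|---|---|---|---|---|
| 20% / 20% | 0.998 | 4.8% | 0.998 | 4.3% |
| 40% / 40% | 0.994 | 5.4% | 0.995 | 4.9% |
| 40% / 20% | 0.896 | 6.6% | 1.008 | 4.2% |
| 20% / 40% | 1.140 | 7.5% | 1.012 | 5.0% |
| 60% / 20% | 0.777 | 13.3% | 1.002 | 4.9% |

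The simulated ratios agree with the formula (at 60% / 20%, 42/54 = 0.778). With a true ratio of 0.70, the offset estimates were 0.691 to 0.699.

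**Step 4: cost of equal loss.** Suppose 25% of time goes unobserved in both arms (half the patients leaving at a mean of Day 30: 15 of 60 days). The ratio is unbiased, but power falls. Power = Φ(|log RR| / √(1/E_C + 1/E_T) − 1.96), where E is the expected event total. For RR = 0.6:

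- Control mean 0.5: totals 25 and 15 give 34.6%; totals 18.75 and 11.25 give 27.2%.
- Control mean 1.0: totals 50 and 30 give 59.9%; totals 37.5 and 22.5 give 48.2%.

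**The case against.** The strongest reply is that nothing in the documents shows unequal observation. The trial is randomized, and with equal loss the factor is exactly 1.00. Moderate imbalance does limited harm: at 40% / 20% the simulated type I error is 6.6%. This stands, and it rules out saying that the result is biased.

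Second, follow-up is promised for 60 days, the retention call makes sense only if follow-up continues after discharge, Appendix A schedules chart abstraction for everyone, and Section 5.3 defers data procedures to a data management plan. The call could well bring events to light. As written, though, its purpose is retention, and the chart it would supplement is the agency's own.

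Third, a reader might infer three stronger things that the documents do not support:

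- *Patients who leave early count as event-free.* Events before exit are recorded, so counts are truncated, not set to zero.
- *Death dates were never collected.* The header of the Appendix C example form is cut off in the text available (falls, which Section 5.1 sends to the form, are not visible either), so absent columns prove nothing. The amendment's composite with death is analysed as time to first event, which needs the timing of deaths.
- *Death is ignored.* That composite handles it in part, although it was added after study completion. Death also differs from lost contact: no later event exists to be missed, and a cumulative count to Day 60 is a legitimate quantity.

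Fourth, an offset corrects only exit unrelated to event risk. Discharge on recovery, or death, is probably related. If those discharged have a lower rate afterwards, Step 1 overstates the bias and the offset would over-correct. This also stands, and it is why complete ascertainment comes before the offset in the remedy.

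**Conclusion.** The concern holds as a gap in ascertainment and analysis that should be closed. The sources, followed as written, can miss primary events after discharge from home health, and the models have no means of allowing for it. The size in this trial cannot be computed because no exit rates are given. Under a constant rate and non-informative exit, the Day 60 ratio is multiplied by 0.94 to 0.83 when 30% to 50% of tested patients leave early against 20% of controls, and by 1.13 with 20% against 40%. Equal loss leaves the ratio alone and costs power, for example 59.9% down to 48.2%. A conclusion that the rate ratio is in fact biased would need evidence that observed time or capture differed by arm, and the documents contain none.

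**What to change.** **Ascertainment.** In Section 3.5, make the planned call a scripted outcome contact at Day 30 and Day 60 for every patient off service, identically in both arms, asking for dates of admissions, ED visits and falls, and vital status. In Section 5.1, name those answers and the chart as the sources, keep the white board only as a prompt, and record an end-of-observation date (death, withdrawal or last outcome contact).

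**Analysis.** In Section 7, add log(days under outcome observation) as an offset to all count models, counting only events inside that time, and censor time to first event at the same date. State when day counting starts, because Section 2.1 times outcomes from discharge while the Protocol Summary follows patients from home health admission. Report home-health discharges, withdrawals and deaths by arm. Handle death through the composite or a sensitivity analysis, because the offset does not correct informative exit.

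**If collection is closed.** The 2016 amendment says the study was complete, so new calls cannot help this dataset. The exit table by arm, the offset and the censoring can still be applied with whatever discharge and death dates are available. An event learned after discharge must not be counted against exposure that stops at discharge.

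**Cost.** A few extra questions in calls already planned, one more date per patient, reliance on some self-reported events, and slightly more analysis.

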## 5.2 Source documents and access to source data/documents

Study staff will maintain appropriate medical and research records for this study, in compliance with ICH E6, Section 4.9 and regulatory and institutional requirements for the protection of confidentiality of subjects. Study staff will permit authorized representatives of regulatory agencies to examine (and when required by applicable law, to copy) research records for the purposes of quality assurance reviews, audits, and evaluation of the study safety, progress and data validity.

## 5.3 Quality control and quality assurance

Details regarding procedures for ensuring high quality data will be specified in the data management plan.

# 6 DATA CONSIDERATIONS

Data collection and accurate documentation are the responsibility of the study staff under the supervision of the investigator. All source documents and laboratory reports must be reviewed by the study team and data entry staff members, who will ensure that they are accurate and complete. Unanticipated problems and adverse events must be reviewed by the investigator or designee.

The investigator is responsible for ensuring the accuracy, completeness, legibility, and timeliness of the data. All source documents should be completed in a neat, legible manner to ensure accurate interpretation of data. The investigator will maintain adequate case histories of study subjects, including accurate case report forms (CRFs), and source documentation.

Study documents should be retained for a minimum of 2 years. These documents should be retained for a longer period, however, if required by local regulations. No records will be destroyed without the written consent of the sponsor, if applicable. It is the responsibility of the sponsor to inform the investigator when these documents no longer need to be retained.

## **7 STATISTICAL CONSIDERATIONS**

The statistical analysis will include the comparison of the YouScript® and control groups the primary and exploratory outcomes. Poisson regression will be used to compare the number of re-hospitalizations at 30 days, the number of re-hospitalizations at 60 days, the number of ED visits at 30 days, the number of ED visits at 60 days and the number of falls. The log-rank test will be used to compare the time to the first re-hospitalization and the time to the first ER visit. OASIS and PHQ-2 scores will be compared using the Wilcoxon rank sum test. The chi-squared test or the Fisher's exact test (as needed) will be used to compare the proportion of cases with acceptance by the study pharmacist and passing on to clinicians and the proportions of recommendations acted on by clinicians. Calculations will be carried out in R (Vienna, Austria). All tests will be two-sided.  $P < 0.05$  will be used to denote statistical significance. As the study is designed as a pilot, tests will not be adjusted for multiple comparisons.

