#### **3.3.2 Enrollment/Baseline**

Any new data will be collected during regularly scheduled nursing visits. Principal investigator will review to verify that subjects continue to meet the eligibility criteria.

- Obtain and document consent from subject on study consent form
- Verify inclusion/exclusion criteria
- Obtain demographic information, medical history, medication history, alcohol, and tobacco use history
- Collect blood/urine/saliva/other specimen
- Record results of selected OASIS metrics and PHQ-2
- For those randomized to intervention:
  - Collect buccal swab for testing

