### **3.4 Randomization Procedures**

Prior to enrollment the treatment assignments were generated as a simple random sample, with 50 patients in each treatment arm. The randomization was carried out in R version 3.1.1 (Vienna, Austria).

Patients will be numbered chronologically by date of enrollment and each number has been randomized *a priori* to a treatment arm as stated above. Nurses are assigned patients based on coverage area and schedule. Only the PI will have access to the randomization list as to avoid any manipulation of patients to different treatment arms.

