## **5 DATA MANAGEMENT CONSIDERATIONS**

### **5.1 Outcome measures**

The following outcome measures will be recorded by the nurse upon patient admission, Day 30, and Day 60. PI will extract the data from patient charts and manually enter the data into the data entry form (Appendix C):

| Endpoint              | Indicator   | Scale                                                                                                                                                                                                                                                                                                                                                                                                                                                                                                                                                                                                                                                         |
|-----------------------|-------------|---------------------------------------------------------------------------------------------------------------------------------------------------------------------------------------------------------------------------------------------------------------------------------------------------------------------------------------------------------------------------------------------------------------------------------------------------------------------------------------------------------------------------------------------------------------------------------------------------------------------------------------------------------------|
| Overall status        | OASIS M1034 | 
0 - The patient is stable with no heightened risk(s) for serious complications and death (beyond those typical of the patient's age).
 
1 - The patient is temporarily facing high health risk(s), but is likely to return to being stable without heightened risk(s) for serious complications and death (beyond those typical of the patient's age).
 
2 - The patient is likely to remain in fragile health and have ongoing high risk(s) of serious complications and death
 
3 - The patient has serious progressive conditions that could lead to death within a year.
 
UK - The patient's situation is unknown or unclear.
 |

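### No baseline covariate is named for the primary count models, although allocation is unstratified and age and admission M1034 are recorded in both arms

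*Combined protocol and SAP*

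**What the plan says.** Section 7 (Statistical Considerations) and its repeat in the separate statistical analysis plan section state that "Poisson regression will be used to compare the number of re-hospitalizations at 30 days". The same sentence covers re-hospitalizations at 60 days, ED visits at both times, and falls. No covariate, stratum or offset is named, and the model is not written out.

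Item 3 of the March 24, 2016 amendments reopened these models. Where a test for over-dispersion was significant, "we used the negative binomial regression instead of the Poisson regression". No covariate was added.

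Section 3.4 describes the assignments as "generated as a simple random sample, with 50 patients in each treatment arm", with no strata, blocks or minimisation.

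Baseline data are available in both arms. Section 3.3.2 requires staff to "Obtain demographic information, medical history, medication history, alcohol, and tobacco use history" and to record the selected OASIS items and PHQ-2; in that list only the buccal swab is confined to the intervention arm. Section 5.1 says the OASIS and PHQ-2 measures "will be recorded by the nurse upon patient admission, Day 30, and Day 60". The example data entry form in Appendix C has columns for age and for M1034 at admission.

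Section 2 also describes propensity-score matching on key characteristics, and Section 3.4.1 mentions matching. Neither fits the randomised design, and Section 7 does not use matching.

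**The concern.** With 100 patients and probably few events, two things follow from comparing arms without baseline risk. A chance difference in risk between arms passes straight into the estimated rate ratio. Between-patient variation in risk that a recorded variable could explain also stays in the error.

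The matching text suggests that the authors wanted key characteristics balanced, yet neither the allocation nor the stated analysis does this. M1034 is a natural candidate: it grades the patient's risk of serious complications and death, and it is recorded at admission. The trial is a pilot, but Section 7 still tests each outcome at a two-sided 5% level, so the precision and credibility of those tests matter.

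**Working it through.** **Inputs from the documents.** 50 patients per arm, two-sided alpha 0.05, follow-up of 60 days. There is no power statement, event rate, target effect or prognostic strength, so the plan has no figure to reproduce.

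**Assumed inputs.** Rate ratio 0.5; control mean mu0 of 0.25 to 1.0 events per patient; covariate effect b of 0.3, 0.5 or 0.7 log-rate per SD (rate ratios of 1.35, 1.65 and 2.01).

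**1. Chance imbalance, binary factor.** If K of 100 patients carry the factor, the number X in one arm is hypergeometric (100, K, 50) and the difference in proportions is (2X - K)/50. The two-sided probability of 15 points or more is:

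- K = 30: 12.6%
- K = 40: 15.3%
- K = 50: 16.1%

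Half of each (6-8%) favours the intervention. If the factor doubles the event rate, a 15-point imbalance centred on prevalence p alone gives a rate ratio of (1 + p - 0.075)/(1 + p + 0.075):

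- p = 0.30: 1.225/1.375 = 0.89
- p = 0.40: 1.325/1.475 = 0.90
- p = 0.50: 1.425/1.575 = 0.90

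**2. Chance imbalance, continuous factor.** The SD of the standardised difference d is sqrt(2/50) = 0.20, so |d| exceeds 0.2 in 32% of trials, and the 95% limit is 1.96 x 0.20 = 0.39. The unadjusted rate ratio is multiplied by exp(b x d): 1.06 to 1.15 at d = 0.2, and 1.12 to 1.32 at d = 0.39, for b from 0.3 to 0.7.

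**3. Precision by formula.** With no other heterogeneity and k = exp(b^2) - 1:

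- unadjusted var(log RR) = 1/(50 mu0) + 1/(50 mu1) + 2k/50
- adjusted var(log RR) = 1/(50 mu0) + 1/(50 mu1)
- power = Phi(ln 2/SE - 1.96)

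Example, mu0 = 0.5, mu1 = 0.25, b = 0.5. The first two terms are 0.04 + 0.08 = 0.12. k = 0.284, so 2k/50 = 0.0114. The SE is sqrt(0.1314) = 0.362 unadjusted and sqrt(0.12) = 0.346 adjusted, and power goes from 48.1% to 51.6%.

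| mu0 | Unadjusted power, b = 0.3 / 0.5 / 0.7 | Adjusted power |
|---|---|---|
| 0.25 | 28.9 / 28.2 / 27.0% | 29.3% |
| 0.5 | 50.4 / 48.1 / 44.4% | 51.6% |
| 1.0 | 78.4 / 73.7 / 66.0% | 80.8% |

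**4. Simulation, one covariate** (3,000 trials per scenario, dispersion-corrected Poisson standing in for the negative binomial). Power, unadjusted to adjusted, for b = 0.3, 0.5 and 0.7:

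- 0.25 events: 24 to 24%, 25 to 24%, 24 to 25%
- 0.5 events: 50 to 51%, 47 to 50%, 44 to 49%
- 1.0 event: 79 to 81%, 76 to 82%, 66 to 79%

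With residual gamma variance 0.5 the change runs from about nil to 14 points. The largest gain (53.5 to 67.8%, at 1.0 event and b = 0.7) comes with null rejection of 6.9% adjusted against 5.4% unadjusted, so part of it is not real.

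**5. Simulation, one or two covariates.** If none is prognostic, power changes by 0 to -1 point. If one is prognostic at b = 0.5, the gain is about 2 points at 0.25 events and 4-7 points at 0.5-0.8 events.

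**6. Where the loss appears.** Under plain Poisson the reported SE hardly moves: 0.287 unadjusted and 0.289 adjusted at 0.5 events, while the true SD of the unadjusted log rate ratio is 0.301, 0.313 or 0.330 as b rises. Omitted risk therefore shows as over-dispersion. Null rejection is 5.5%, 6.2% and 7.8% at 0.5 events, and 5.8%, 8.3% and 12.4% at 1.0. It widens the interval only under a dispersion-corrected model.

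**The case against.** The strongest reply is that an unadjusted comparison of randomised arms is valid, that a correctly sized test already allows for chance imbalance, and that a pilot with no power claim need not seek efficiency. All of that stands. A reader might infer that the comparison is biased or the test invalid because covariates are absent; the documents do not support this. The over-dispersion in step 6 is a matter of the error model, and the negative binomial switch addresses it at least in part. The switch neither corrects imbalance nor recovers precision.

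A reader might also infer that strong predictors were ignored. No figure in the documents links age, M1034 or number of drugs to re-hospitalization or ED visits. The appended risk form scores age only as 65 or over, which every participant meets, and M1034 is not on that form. The prognostic strength is assumed throughout.

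Two further points stand. Two of the four primary outcomes are 30-day counts, with means no higher than at 60 days, where the gain may be nil. And the choice of covariates is open to argument: recent hospitalization and drug count are also plausible, but neither has a column on the example form, and sparse counts do not support a long list. This argues for one or two values already recorded, not against adjustment. The shift from a 15-point imbalance (log 0.89, about -0.12) is also only about a third of an SE of about 0.35.

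**Conclusion.** The point holds as a modest weakness in efficiency and robustness. No covariate is named for the count models in Section 7 or in the amendments. That the models contain arm alone is inferred from this silence, so the plan should at least say whether they are adjusted.

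The 13-16% chance of a 15-point imbalance rests only on 50 per arm and the assumed prevalence. The power gain rests wholly on assumed event rates, a rate ratio of 0.5 and assumed prognostic strength. It is about nil at 0.25 events per control patient or with non-prognostic covariates, and roughly 4-7 points at 0.5-0.8 events with b = 0.5. It can be larger with stronger covariates, but no single figure can be claimed for this trial.

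**What to change.** For the four primary counts and falls, fit the planned Poisson model, or the negative binomial where over-dispersion is found as in the amendments, with arm plus a short fixed list:

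- admission M1034, as a linear score from 0 to 3, with the unknown category given a stated code so that no patient is dropped;
- age.

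Report the unadjusted model beside it, and add no further covariates given the few events expected. Because the analysis plan was already amended after study completion, an adjusted model added at that stage should be labelled post hoc. The matching text in Sections 2 and 3.4.1 should be reconciled with the randomised design at the same time.

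The cost is a sentence or two in the plan and one or two extra parameters per model, with no new data. The downside is almost no gain when events are few, and up to about one point of power lost if neither covariate is prognostic.
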